## Abstract

**Background:**

Over the last years, less invasive surgical techniques with soft tissue preservation for bone conduction hearing implants (BCHI) have been introduced such as the linear incision technique combined with a punch. Results using this technique seem favorable in terms of rate of peri-abutment dermatitis (PAD), esthetics, and preservation of skin sensibility. Recently, a new standardized surgical technique for BCHI placement, the Minimally Invasive Ponto Surgery (MIPS) technique has been developed by Oticon Medical AB (Askim, Sweden). This technique aims to standardize surgery by using a novel surgical instrumentation kit and minimize soft tissue trauma.

**Methods:**

A multicenter randomized controlled trial is designed to compare the MIPS technique to the linear incision technique with soft tissue preservation. The primary investigation center is Maastricht University Medical Center. Sixty-two participants will be included with a 2-year follow-up period. Parameters are introduced to quantify factors such as loss of skin sensibility, dehiscence of the skin next to the abutment, skin overgrowth, and cosmetic results. A new type of sampling method is incorporated to aid in the estimation of complications. To gain further understanding of PAD, swabs and skin biopsies are collected during follow-up visits for evaluation of the bacterial profile and inflammatory cytokine expression.

The primary objective of the study is to compare the incidence of PAD during the first 3 months after BCHI placement. Secondary objectives include the assessment of parameters related to surgery, wound healing, pain, loss of sensibility of the skin around the implant, implant extrusion rate, implant stability measurements, dehiscence of the skin next to the abutment, and esthetic appeal. Tertiary objectives include assessment of other factors related to PAD and a health economic evaluation.

**Discussion:**

This is the first trial to compare the recently developed MIPS technique to the linear incision technique with soft tissue preservation for BCHI surgery. Newly introduced parameters and sampling method will aid in the prediction of results and complications after BCHI placement.

**Trial registration:**

Registered at the CCMO register in the Netherlands on 24 November 2014: NL50072.068.14. Retrospectively registered on 21 April 2015 at ClinicalTrials.gov: NCT02438618. This trial is sponsored by Oticon Medical AB.

**Electronic supplementary material:**

The online version of this article (doi:10.1186/s13063-016-1662-0) contains supplementary material, which is available to authorized users.

## Background

The World Health Organization estimated that approximately 360 million people worldwide suffer from disabling hearing loss (HL) [1]. People with HL can often benefit from the use of hearing devices, such as hearing aids, but patients with, e.g., conductive hearing loss cannot always profit from traditional hearing aids. In order to improve hearing for this group of patients, the bone-anchored hearing aid (BAHA), also known as the bone conduction hearing implant (BCHI) was introduced in 1981 [2]. The BCHI consists of a titanium fixture implanted in the retroauricular bone of the skull with an abutment that breaches the skin, so that a sound processor can be attached to it. The sound processor converts sound waves into vibrations via its transducer. These vibrations are conducted by the abutment to the titanium fixture and ultimately to the skull. The skull conducts these vibrations to both inner ears, bypassing any problems in the ear canal or middle ear [3]. BCHIs are currently considered a suitable treatment option for three groups of patients, namely patients with conductive HL, mixed HL or single-sided deafness (SSD).

This technology has been reported to improve the quality of life for these patients, although the available data is limited [4, 5]. Recently, measuring quality of life and wellbeing using the concept of capabilities has gained more interest [6]. It can be expected that interventions that entail placing a percutaneous implant to improve hearing, may influence an individual in more ways than just solely altering hearing (e.g., the ability to participate in society versus the perceived disadvantages of these types of implants such as cosmetic and social concerns [7, 8]). This perspective will be considered in this trial as well. Over the years, the BCHI has become an established treatment option with approximately 200,000 BCHI surgeries worldwide to date [9].

Although successful, the BCHI has complications. Known problems include skin inflammation, also known as peri-abutment dermatitis (PAD), pain, numbness of the skin around the implant, skin overgrowth, and implant loss [10]. PAD is graded on a five-point scale called the Holgers Index [11] and is perceived as the most common complication of BCHI use with an estimated occurrence of 16.1–38.1 % among all recipients [10]. PAD is an inflammatory process that is presumed to be multifactorial and little is known about the precise etiology of this condition [12]. Shear stress on the skin around the abutment [2, 13] sets on as the implant and abutment combination fixed to the skull is immovable. This may cause tearing of the skin (e.g., while turning on a pillow at night or during head and jaw movements). The implant and abutment are made of titanium, which may elicit a foreign body response [12, 14]. Also the formation of a biofilm on the abutment by bacteria that colonize the wound site due to persistent breach of the skin might play an important role [15, 16]. Another side effect of the BCHI is pain. This is frequently experienced by patients [17], however the exact cause for this, sometimes chronic pain, remains unknown [18–20]. Another condition which has anecdotally been observed is skin sagging, the presence of excess skin cranially to the abutment [21]. This might be problematic as it can influence the sound processor coupling and the proper function of the processor.

Various strategies for reducing complication rates with BCHIs have been employed throughout the years. Traditionally, the skin surrounding the abutment was thinned, but van de Berg et al. noted lower complication rates after BCHI surgery with a less invasive approach [20]. Since then, an even less invasive, single-stage procedure, where the soft tissue surrounding the abutment is left intact [22–25], has become one of the most common techniques used for BCHI surgery. Advantages of this tissue-preserving approach include: less surgical procedure time, reduced numbness or pain and better cosmetic results [22, 24, 25].

The osteotomy preparation, assuring minimal trauma to the bone, space to maneuver the burr head, and adequate cooling of the site as well as minimal trauma and displacement of the soft tissue, are all important factors when designing a procedure for installing a bone-anchored percutaneous implant [26]. Furthermore, to achieve comparable results across surgeries, the variation in surgical technique introduced by different surgeons needs to be minimized. Based on local clinical practices and available tools, surgeons in different countries have started using punch-only surgical techniques for BCHI surgery [27–29]. The available surgical tools were not developed for this punch-only approach, presenting potential drawbacks such as soft tissue damage and insufficient irrigation. In pursuance of developing a standardized minimally invasive punch-only surgical kit and method, Oticon Medical AB (Askim, Sweden) started the design of instruments for a single-stage BCHI surgical technique in 2013. The goal of this new Minimally Invasive Ponto Surgery (MIPS) was to optimize tissue preservation, minimize tissue trauma, and provide a punch-only standardized surgical procedure with standardized surgical equipment aiming to eliminate surgical variability [26].

Previous BCHI clinical trials used non-validated outcome measurement scales, creating a need for validated alternatives. Most questionnaires and endpoints currently used to evaluate the BCHI from the perspective of the clinicians rather than that of the patients’ [30]. We know that studies using non-validated scales are prone to risk of bias [31]. In contrast, studies that use reliable, systematic and validated outcome measures give the possibility to compare different trials and perform a meta-analysis [32]. Another limitation is that the number of prospective randomized controlled trials in the field is low [22, 33–36]. Moreover, complications related to the BCHI can vary over time and may be missed by only assessing patients at fixed time points coinciding with preplanned trial visits. Important information is lost this way and incidence numbers might become under- or overestimated. By not collecting all the information which is available, the ability to find a difference between two interventions also decreases. In this clinical trial, the amount of standard visits is decreased in favor of collecting more information during extra consultations in case of problems.

The decision to choose one intervention over the other in a health care system *with limited resources* depends on the associated (clinical) benefits, but also on the incurred additional costs or cost savings. As reviewed by Crowson et al. [4], only a few investigations addressed the cost-effectiveness of a BCHI intervention, resulting in uncertainty regarding cost-effectiveness. One retrospective study by Monksfield et al. has been executed in the United Kingdom that compared gain in quality-adjusted life years to BCHI-related costs. Costs included: implantation surgery, post-surgical care, the first processor, annual check-up, processor maintenance, and processor replacement costs after 3 years [5]. This study concluded that the BCHI is probably cost-effective. So far, no study included non-health care costs, such as loss of productivity, travel costs and out-of-pocket costs.

In this article, we describe the research protocol for a multicenter randomized controlled study comparing the new MIPS technique to the linear incision technique with soft tissue preservation [24, 26] comparing the incidence of inflammation as primary objective. In this trial, revised parameter scales are introduced to quantify factors such as loss of skin sensibility, dehiscence of the skin next to the abutment, skin overgrowth, and cosmetic results. These are modified to reduce the subjective interpretation and are intended to be validated. For exploratory outcome measures related to PAD such as skin biopsies, bacterial swabs are collected. An economical evaluation is planned with quality of life approached from a capability perspective as well. The MIPS technique is hypothesized to result in a lower incidence of inflammation compared to the linear incision technique with soft tissue preservation.

## Methods

### Study design, ethics, setting, and recruitment

This study is a sponsor-initiated multicenter, open, randomized, controlled clinical investigation. This article has been drafted following SPIRIT guidelines [37] (See Table 1 in Additional file 1). Three hospitals in the Netherlands are currently recruiting participants for this study: Maastricht University Medical Center (MUMC+), ZiekenhuisGroep Twente (ZGT) and Medisch Centrum Leeuwarden (MCL). MUMC+ is an academic teaching hospital. ZGT and MCL are general hospitals. This multicenter study is performed in accordance with the Declaration of Helsinki [38], has been approved by the ethics committee of MUMC+ (NL50072.068.14/METC141007) and has been registered at clinicaltrials.gov (trial number: NCT02438618). The local ethics committees of ZGT (Adviescommissie locale uitvoerbaarheid wetenschappelijk onderzoek) and MCL (Commissie Onderzoeksverklaring) approved the local execution of this trial. A total of 62 participants will be recruited at the ear, nose and throat outpatient departments by the (local) researchers. Patients are considered eligible for participation [22, 39] (I) if they will undergo unilateral BCHI surgery and (II) when they are ≥ 18 years of age. Participants will be excluded from participation in case of (I) a history of immunosuppressive disease, (II) usage of systemic immunosuppressive medication, (III) bilateral BCHI placement, (IV) relevant dermatological disease (e.g., psoriasis, severe eczema), (V) participation in other studies, and (VI) when no suitable site for a 4-mm-wide implantation during surgery is found. For inclusion, written informed consent will be provided from all participants (See Additional file 2).

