### Study interventions and allocation

All participants will undergo single-stage surgery to receive a 4-mm Ponto wide implant with mounted abutment (Oticon Medical AB, Askim, Sweden), which will be performed by an experienced ENT surgeon. Four abutment lengths are available: 6, 9, 12 and 14 mm. Subjects will be randomized to the test group (MIPS technique [26]) or the control group (linear incision technique with soft tissue preservation [24]) in the order in which they enter the study. Skin thickness is a possible factor that could influence inflammation, but this is measured during surgery, making it impossible to stratify for skin thickness prior to surgery. Considering that men are known to have significantly thicker skin than women [40], group allocation is stratified for gender. Researchers will randomize each subject using randomization software (Statistiska Konsultgruppen, Gothenburg, Sweden), which will be performed in each research center independently in a 1:1 ratio for the test and control group stratified for gender until the total number of 62 participants has been reached. Due to clear differences in surgical techniques, it is impossible to blind the surgeon, researcher or subject. In short both surgical techniques are described here:

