#### Control group (linear incision technique with soft tissue preservation) [24, 41]

The intended implant position is marked (Fig. 1a). (I) A retroauricular linear incision is made down to the periosteum that is subsequently opened to expose the periosteum posterior to the incision line (Fig. 1b). (II) At the intended implant site, a central area of periosteum is removed. (III) An initial 3-mm-deep hole is created using a guide drill. (IV) If there is still bone at the bottom of the initial hole, it is deepened to 4 mm using the same drill by removing a spacer. (V) To prepare the initial hole for implant insertion it is widened with a countersink drill. (VI) The implant with mounted abutment is installed with a torque setting of 40–50 Ncm. (VII) The skin is retracted over the abutment and dermal sutures are placed. (VIII) The abutment is recovered by punching the skin with a 5-mm punch. (IX) A healing cap is attached to the abutment and gauze drenched in an antibiotic ointment is applied.

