#### Test group (MIPS technique) [26, 42]

The intended implant position is marked (Fig. 1a). *(I)* An incision is created with a 5-mm punch at the intended implant site (Fig. 1c). *(II)* The periosteum and remaining soft tissue around the incision hole are removed with a raspatorium. *(III)* The cannula is inserted at the surgical site. *(IV)* A 3-mm hole is created initially with the cannula guide drill. *(V)* If there is bone at the bottom of the 3-mm hole, it is deepened to 4 mm using the same drill by removing a spacer*. (VI)* To prepare the initial hole for implant insertion, it is widened with the cannula widening drill. *(VII)* The cannula is removed and subsequently the implant with mounted abutment is installed with a torque setting of 40–50 Ncm*. (VIII)* To help estimate complete insertion of the implant, an installation indicator is attached to the abutment inserter, which makes it possible for the surgeon to count the number of rotations. This step was added during the course of the study. *(IX)* A healing cap is attached to the abutment and gauze drenched in an antibiotic ointment is applied.

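### Exclusion criterion VI is applied during surgery, after randomisation, by a surgeon who knows the arm, so it could remove participants unequally from the comparison

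*Protocol article*

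**What the plan says.** In the protocol article, Methods, the section on study design, ethics, setting and recruitment lists six exclusion criteria under the lead-in "Participants will be excluded from participation in case of". The sixth applies "when no suitable site for a 4-mm-wide implantation during surgery is found".

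The section on study interventions and allocation states: "Subjects will be randomized to the test group" or to the control group, and this happens "in the order in which they enter the study". It explains why skin thickness was not a stratification factor: "this is measured during surgery, making it impossible to stratify for skin thickness prior to surgery". On blinding it says that "it is impossible to blind the surgeon, researcher or subject".

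The two techniques reach bone differently. Control: "A retroauricular linear incision is made down to the periosteum that is subsequently opened to expose the periosteum posterior to the incision line". MIPS: "An incision is created with a 5-mm punch at the intended implant site", followed by drilling through a cannula. In both arms the intended position is marked first, and a 3-mm hole is deepened to 4 mm if bone remains at its base.

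**The concern.** Eligibility criteria are normally settled before allocation, so that the two groups differ only by chance. Criterion VI cannot be settled then. If it is followed as written, a participant who has been randomised and has had the assigned operation started is taken out of the trial on a judgement made by an operator who knows the arm.

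Two things are at stake. First, the 3-month Holgers outcome of such a participant may never be collected, and no later analysis rule can recover it. Second, if exclusions are more frequent in one arm, or fall on different kinds of patient in each arm, the remaining groups are no longer those created by randomisation. Failure to find a site is also information about a surgical technique that a trial of a new technique should show by arm.

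**Working it through.** **Step 1: order of events.**
- Allocation comes before surgery. The article's reason for not stratifying on skin thickness (known only during the operation) makes sense only if allocation is already done by then.
- Criterion VI is judged during surgery, hence after allocation.
- Bone is reached only after the linear incision (control) or the punch (MIPS), hence after the allocated technique has begun.
- The surgeon knows the arm.

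These four statements come from the text and need no outside source.

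**Step 2: could the chance of exclusion differ by arm?**
- For a difference: control exposes periosteum through an opened incision, while MIPS works through a punch and cannula at the intended site. The scope to look for another site may differ.
- Against: the marked position, the 3-mm then 4-mm depth check and the implant are the same in both arms, so failure at the first site may be similar.
- The documents give no frequency for criterion VI in either arm. A difference is possible but not shown.

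**Step 3: the article's sample size (Sample size calculation section).**
- Inputs: z values 1.65 and 0.84, h = 0.65, drop-out 5%.
- n = 2(1.65 + 0.84)² / 0.65² = 12.40 / 0.4225 = 29.35 per group. Then 29.35 / 0.95 = 30.9, so 31 per group and 62 in total. The stated figure reproduces. The value 1.65 is a one-sided 5% point.
- Headroom: 31 × 0.95 = 29.45 against 29.35 needed. The 5% allowance is 0.05 × 31 = 1.55 participants per arm, and one exclusion is 1/31 = 3.2% of an arm. Nothing is set aside for exclusions in theatre.

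**Step 4: power after further losses.** Power = Φ(h·√[n₁n₂/(n₁+n₂)] − z), starting from 29 per arm after drop-out, with k more lost from one arm.

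| k | n₁, n₂ | One-sided 0.05 (article's basis) | Two-sided 0.05 |
|---|---|---|---|
| 0 | 29, 29 | 79.7% | 69.7% |
| 1 | 28, 29 | 79.1% | 68.9% |
| 2 | 27, 29 | 78.4% | 68.1% |
| 3 | 26, 29 | 77.7% | 67.2% |
| 4 | 25, 29 | 76.9% | 66.3% |

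The drop for four losses is 2.8 points one-sided (3.4 two-sided).

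**Step 5: possible bias (illustration only).** Assumptions: no true effect; the 16.1–38.1% occurrence in the Background section is taken as the 3-month risk p in both arms; k of 31 are removed from the MIPS arm only; those removed would have had risk r. Observed MIPS rate = (31p − kr) / (31 − k).

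| Assumed r | Fall in observed MIPS rate, k = 1 to 3, p = 16.1% | Same, p = 38.1% |
|---|---|---|
| equal to p | 0 | 0 |
| 60% | 1.5 to 4.7 points | 0.7 to 2.3 points |
| 100% (upper bound) | 2.8 to 9.0 points | 2.1 to 6.6 points |

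Example: p = 16.1%, k = 3, r = 60% gives (4.991 − 1.8) / 28 = 11.4%, a fall of 4.7 points. For scale, h = 0.65 corresponds to 16.1% versus 0.8% (15.3 points) or 38.1% versus 11.1% (27.0 points). The table concerns only participants who would still have had an abutment, since the Holgers grade describes skin around one.

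**The case against.** The strongest reply is that the article fixes no analysis set. It leaves the method of analysis for each endpoint to a SAP that is not shown, and that SAP may keep every randomised participant. This stands in part: a reader might infer that excluded participants are dropped from all results, and the article does not say so. It does not dispose of the point, because criterion VI is a stated rule rather than an omitted detail. A SAP can define who is analysed, but it cannot supply an outcome for someone who was taken out of participation and not followed.

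A reader might also infer that exclusion depends on the technique. The texts show different exposure but the same marking and depth check, so only a possible difference is supported.

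A further tempting reading is that the rule hides failures of the new technique. The Safety section has adverse events and device deficiencies recorded and carried into the results, and the Limitations section promises a qualitative assessment of (serious) adverse events to find drawbacks. These do not guarantee a count of no-site cases by arm, but they do not support concealment either. Conversion from one technique to the other is mentioned nowhere, and the point does not rest on it.

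Finally, all participants are meant to receive the 4-mm wide implant, so someone may defensibly want the effect in that group alone. This stands as a reason for a supplementary analysis, not for removing people after randomisation.

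**Conclusion.** The point holds in a limited form. Criterion VI is an exclusion after randomisation, made by an unblinded operator once the allocated technique is under way. Following it risks losing primary outcomes and leaving two groups that are no longer the randomised ones.

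How much this matters cannot be derived from the documents. The bias is zero if those excluded resemble the rest of their arm, or several percentage points under deliberately unfavourable assumptions about number, arm and risk. The effect on power is minor. With an unknown frequency, an unproven arm difference and an unseen SAP, this is a moderate concern that is worth correcting because the correction is cheap.

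**What to change.** 1. Do not apply criterion VI as an exclusion once a participant has been randomised.
2. Keep every randomised participant who receives a percutaneous implant in follow-up and in the primary analysis, in the allocated arm. Add a sensitivity analysis restricted to the 4-mm wide implant.
3. Report participants left without an implant by arm, as a surgical outcome. Imputing dermatitis for them would have little meaning, since there is no abutment.
4. Report by arm any criterion VI exclusions already made. Recruitment was still open when the article was written, so follow-up could be preserved for later cases.

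The cost is a wording amendment to the protocol and matching SAP text. A few participants with a non-standard implant stay in the primary analysis and add slight noise. No surgical step changes.
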